### 12.3 Statistical analysis:

**Descriptive Analyses & Missing Data.** Descriptive analyses will include family demographics, biomarker, child and caregiver health, and family social needs. Data will be inspected for outliers and out-of-range values. Examination of distributions may prompt transformations, where they are defensible and are a component of the best available analysis strategy. Although protocols have been designed to promote retention, some attrition is inevitable. We will perform analyses to determine whether differential attrition occurred by patient characteristics. Likelihood based approaches (e.g. GLMMs) will be used to handle missing data. This approach fits models to all available data and invoke the relative assumption that the data are missing at random.

Background demographics will be examined to describe the sample and will be included in multivariate analysis if they are related to the outcome at  $p < .2$  or associated with dropout. Correlations among variables will be examined and redundant measures will be combined or eliminated to avoid multicollinearity. We will compare participants randomized to the two groups on caregiver and child characteristics using t-tests and chi-square tests.

**Assessment of Outcomes:** We will fit regression models for cross-sectional and longitudinal outcomes. Changes from baseline to follow-up on the primary outcomes will be estimated with linear mixed models and generalized linear models with generalized estimating equations (e.g., SAS PROC MIXED, GENMOD, SAS Institute Inc., 1999). Generally, we seek to model longitudinally the trajectory of the primary outcomes as a function of time. We begin by fitting *base* models, those with intervention group and minimum covariates and, for longitudinal models, the most restricted residual covariance structures. We will then consider additional baseline demographic or family predictors, and baseline family predictors-by-time interaction in subsequent models to examine moderators of change. Similar models will be used to examine each of the primary outcomes outlined. Empirical contributions to model selection decisions will include reference to information criteria (e.g., Akaike's). We will examine change from baseline for each outcome as the dependent variable.

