### 14.4 Explain how and why the number of subjects was chosen (Help Text updated 9/13):

Total enrollment for this phase will not exceed 724 dyads (724 caregivers + 724 children) Power Analysis. Sample size and power estimates are based on alpha = 0.05 and 2-sided t-tests on between group differences in change from baseline to follow-up between the two groups. Estimates of means (SDs) at follow-up from related studies and our own previous work suggest effect sizes that are small to moderate, with 0.26 to .43 SD unit differences for primary parent-reported outcome of number of social needs and 0.38 to 0.46 SD unit differences for change in cortisol. A total sample of 724 dyads (n=362 per arm) will provide power to exceed 0.80 for tests on all primary outcomes. We conservatively estimate a 30% attrition rate over the course of the study, resulting in a final sample of 506 dyads post attrition (n=253 per arm). The study is powered at least 80% to detect small/medium effect sizes of d=.25 or greater. This sample size allows at least 80% power to detect estimated mean differences of changes from baseline of magnitude 0.50 or greater for our likert based primary outcome of number of social needs.

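### Section 12.3 analyses change from baseline without naming the baseline value as a covariate, and section 14.4 does not say which SD its d = 0.25 refers to

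*Protocol*

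**What the plan says.** On the analysis, section 12.3 states: "We will examine change from baseline for each outcome as the dependent variable". The models are linear mixed models and generalized linear models with GEE. The base models hold the study arm and a minimal, unspecified set of covariates. The predictors to be considered afterwards are baseline demographic and family variables and their interactions with time, to look for moderators. The baseline value of the outcome itself is neither named nor ruled out as a covariate. Section 16.1 has the baseline survey and samples completed before randomization, and stratifies randomization by language (English or Spanish).

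On power, section 14.4 bases the calculation on "2-sided t-tests on between group differences in change from baseline to follow-up between the two groups" at alpha 0.05. It then says: "Estimates of means (SDs) at follow-up from related studies and our own previous work suggest effect sizes that are small to moderate". The first range that follows is "0.26 to .43 SD unit differences for primary parent-reported outcome of number of social needs". The second, unlike the first, is labelled as change: "0.38 to 0.46 SD unit differences for change in cortisol". With 253 per arm after 30% attrition it concludes: "The study is powered at least 80% to detect small/medium effect sizes of d=.25 or greater". For social needs it adds "at least 80% power to detect estimated mean differences of changes from baseline of magnitude 0.50 or greater". No SD of change and no baseline/follow-up correlation is given.

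**The concern.** There are two linked weaknesses.

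The first is efficiency. Subtracting the baseline is the best use of it only when the regression slope of follow-up on baseline is 1. With equal SDs that slope is rho, so below rho = 1 a comparison of unadjusted change scores is noisier than one that adjusts for baseline. Below rho = 0.5 it is noisier even than comparing the follow-up values alone. The mixed-model wording does not settle the matter. With two visits and a separate baseline mean in each arm, the arm-by-time contrast in complete pairs is simply the difference in change. Adjustment arises only if baseline enters as a covariate or the arms share a baseline mean, and neither is stated.

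The second is the scale of d. The test is on change, but the only SDs that 14.4 cites are at follow-up. The two SDs coincide only at rho = 0.5 (equal SDs). The sample has almost no margin at d = 0.25, so the choice of SD decides whether 80% is reached there.

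**Working it through.** **Inputs from section 14.4:** two-sided alpha 0.05; 253 per arm analysed; d = 0.25; social-needs effects 0.26 to 0.43; a social-needs difference in change of 0.50. **Assumed, because the protocol gives no figure:** rho, shown over a range, and equal SDs at both visits unless stated.

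**Step 1: reproduce the plan's figure.** 362 x 0.70 = 253.4, so 253 per arm. The noncentrality is 0.25 x sqrt(253/2) = 2.81 on 504 degrees of freedom. Power is 0.801 (noncentral t; 0.803 by the normal approximation). The smallest d with 80% power is 0.2496. The stated figure is therefore correct if d is in units of the SD of the variable tested, which is change.

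**Step 2: put d in follow-up SD units.**
- SD of change = SD x sqrt(2(1 - rho)), so the effective d is d / sqrt(2(1 - rho)).
- The ANCOVA residual SD = SD x sqrt(1 - rho²), so the effective d is d / sqrt(1 - rho²).
- Variance ratio, ANCOVA to change = (1 - rho²) / (2(1 - rho)) = (1 + rho)/2.

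At d = 0.25 and 253 per arm:

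| rho | effective d, change | power, change | effective d, ANCOVA | power, ANCOVA | (1 + rho)/2 |
|---|---|---|---|---|---|
| 0.2 | 0.198 | 0.60 | 0.255 | 0.82 | 0.60 |
| 0.3 | 0.211 | 0.66 | 0.262 | 0.84 | 0.65 |
| 0.5 | 0.250 | 0.80 | 0.289 | 0.90 | 0.75 |
| 0.7 | 0.323 | 0.95 | 0.350 | 0.98 | 0.85 |

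Completers needed per arm for 80% power at d = 0.25 (normal approximation): for unadjusted change 402, 352 and 252 at rho 0.2, 0.3 and 0.5; for ANCOVA 242, 229 and 189. The plan has 253.

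**Step 3: the correlation needed for 80% with unadjusted change.** Minimum rho = 1 - (d/0.2496)²/2.
- d = 0.25: 0.498
- d = 0.26: 0.457
- d = 0.30: 0.28
- d = 0.2496 x sqrt(2) = 0.353 or more: no threshold. At d = 0.43, power is 0.93 even at rho = 0.

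**Step 4: unequal SDs.** Let k be the ratio of baseline to follow-up SD. The variance of change, in units of the follow-up variance, is 1 + k² - 2 x rho x k. It is at most 1 when rho is at least k/2. At d = 0.25 the threshold is then about 0.40 for k = 0.8 and 0.63 for k = 1.25.

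**Step 5: put d in SD-of-change units instead.** Unadjusted power is 0.80 at any rho. The ANCOVA effective d is d x sqrt(2/(1 + rho)), which is never below d, so ANCOVA also keeps at least 80%. The 0.50 difference divided by 0.25 implies an SD of 2.0. On this reading that is the SD of change, but 14.4 does not state it.

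**The case against.** A reader might infer that the 80% power fails unless rho is at least 0.5. Section 14.4 does not support that. It defines the test on change and gives its last target as a difference in changes, so d = 0.25 may well be in SD-of-change units, and then rho is irrelevant to the claim. The reference to follow-up SDs introduces the cortisol range as well, which is labelled as change, so that phrase may be loose wording. This stands, and it cannot be settled from the protocol. It does not prove the favourable reading either: under randomization the expected difference in change equals the expected difference at follow-up, so the 0.50 target does not identify the SD.

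Even on the follow-up-SD reading, 0.5 is the threshold only at d = 0.25 with equal SDs, and 0.25 lies just below the quoted social-needs range. The protocol also gives no evidence that rho is low for social needs or cortisol. A follow-up visit 5 to 9 months after an urgent-care visit makes a low value possible, not established.

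A reader might also infer that the plan excludes baseline adjustment, or that change scores give a biased answer. Neither follows. Section 12.3 is silent on the baseline covariate, and a common-baseline mixed model would fit its wording. Under randomization the unadjusted change score is unbiased: regression to the mean affects both arms alike in expectation, and chance baseline imbalance costs precision rather than validity.

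**Conclusion.** The point holds as a matter of efficiency and of an undefined effect-size scale, not as an error in the stated power. Section 12.3 commits to change as the dependent variable and leaves out the covariate that would use the pre-randomization value best. With equal SDs, ANCOVA needs 60% to 85% of the change-score sample for rho from 0.2 to 0.7.

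The power claim depends on which SD was meant. In SD-of-change units, the 80% stands. In follow-up SD units with equal SDs, unadjusted power at d = 0.25 is 0.60 to 0.80 for rho from 0.2 to 0.5, and the upper part of the quoted social-needs range (about 0.35 to 0.43) is safe at any non-negative rho. A baseline-adjusted analysis gives at least 80% at d = 0.25 on either reading. Rho and the equality of SDs are assumptions here. The change should be made, but nothing in the trial's validity turns on it.

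**What to change.** In section 12.3, state that each continuous outcome is analysed as its 6-month value, with its baseline value and the randomization language stratum as covariates. Two alternatives serve equally well: keep change as the dependent variable and add the same covariates, which gives the same treatment estimate, or use the two-visit model with a common baseline mean for both arms.

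In section 14.4, say whether d = 0.25 is in follow-up SD or SD-of-change units, give that SD for social needs together with any available estimate of rho, and state that the power is for the baseline-adjusted analysis.

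The cost is wording only: no new data, no more participants, and one extra degree of freedom for the baseline covariate, which is negligible at 253 per arm.

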### 12.4 If this study has undergone scientific or scholarly review, please indicate which entity performed the review:

- ☐ Cancer Center Protocol Review Committee (PRC) (Full approval is required prior to final CHR approval for cancer-related protocols.)
- ☐ CTSI Clinical Research Center (CRC) advisory committee
- ☐ Departmental scientific review
- ☐ Other:

Specify **Other**:

---

## 13.0 Background

### 13.1 Background:

Adverse social circumstances like hunger and food insecurity can have dramatic, negative impacts on the health of vulnerable children.(1-5) In safety-net settings, the prevalence of these adverse social circumstances are alarmingly high.(6-7) A 2007 study from Boston Medical Center pediatric emergency department found that over 97% of presenting families had at least one basic social need; over 48% of families reported that within the last 12 months they had either been threatened with or experience utility shut-offs; and over 30% of families said that they had either reduced the size of their meals or skipped meals because they did not have enough money for food.(8) In a study in pediatric urban primary care clinics, over 82% of families reported a least one social need.(9)

Despite the preponderance of social need in both emergency room and primary care safety net settings, the current standard of practice in pediatric medicine fails to address many of the health-related social problems of struggling families. Garg et al. (2007) showed significant gaps between primary care providers' beliefs that they should include social screening topics in pediatric visits and routinized social screening behaviors.(10) Other researchers have demonstrated that comprehensive social screening (across multiple social domains) is particularly rare in pediatric settings.(9)The evidence suggesting irregular and informal screening for health-related social needs belies studies demonstrating that conducting social screening informally during clinical encounters poorly estimates prevalence; providers routinely underestimate social needs in all areas except drug and alcohol use and need for nursing home placement.(11) Furthermore, standardized screening has been shown to be more sensitive than provider clinical interviews.(12)

There is growing evidence that patients who receive public benefits may have better health status and decreased emergency room utilization.(13-19). Despite this emerging literature that serves as important background for FIND implementation, existing intervention programs to address social factors in pediatric clinical settings (e.g. healthleadsusa.org) have not yet included scientific evaluations in either emergency room or primary care settings of program impacts on pediatric health care status or health care utilization, nor on patient satisfaction/connectedness to health care organizations. As a result of conducting a randomized controlled clinical trial, we hope to prove that by systematically addressing our families social determinants of health, we will better connect families to community resources, use healthcare resources more appropriately, improve health status and enhance patient satisfaction.

The San Francisco General Hospital (SFGH) Health Advocacy (HA) intervention specifically includes implementing a navigation desk at the SFGH pediatric urgent care center. The program is available to all families presenting for care to the SFGH Primary Care Clinic. All families entering the site are offered screening for social issues affecting their health, including nutrition, housing and financial insecurity. Families with a positive screen are referred to the HA program, where navigators assist them to address each family's specific needs. Using a client management database, HA navigators follow the family over time to ensure that identified needs have been successfully addressed. The initial RCT data collection effort of the HA intervention was very successful. Results showed that participants in the intervention arm decreased needs and improved child health significantly more than the control group arm (publication pending). In this new study phase, we plan to examine the effects of the HA program on a more robust set of survey data including detailed measures of caregiver and child health and non-invasive biological data. We will collect survey responses to a broader range of health outcomes for children and their caregivers, including intermediate health outcomes like caregiver depression, work and school attendance, and biomarkers of stress IL-6/ inflammatory cytokines (oral swab collection) and hair cortisol. This work is based on existing studies showing that hair cortisol and inflammatory cytokines are important markers of socioeconomic status and social stressors.(20-23)

### 13.2 Preliminary studies:

Patient surveys at SFGH have shown that almost 50% of families accessing care in the primary care clinics have experienced food insecurity over the last 12 months. This population is expected to be assisted with the SFGH HA intervention. The phase one RCT research on CCLiP showed that 50% of intervention families decreased by at least one social need and many decreased more than that; the study also shows a .35 point (on a five point scale) improvement on parent reported child health in comparison with the control group. These findings are comparable to other new studies showing that social needs interventions are successful at promoting referrals to community resources. (24)

## 14.0 Sample Size and Eligibility

### 14.1 Number of subjects that will be enrolled at UCSF and affiliated institutions:

1448

### 14.2 Total number of subjects that will be enrolled at all sites (Help Text updated 9/13):

1448

### 14.3 Estimated number of people that you will need to consent and screen here (but not necessarily enroll) to get the needed subjects:

3000

### 14.4 Explain how and why the number of subjects was chosen (Help Text updated 9/13):

Total enrollment for this phase will not exceed 724 dyads (724 caregivers + 724 children) Power Analysis. Sample size and power estimates are based on alpha = 0.05 and 2-sided t-tests on between group differences in change from baseline to follow-up between the two groups. Estimates of means (SDs) at follow-up from related studies and our own previous work suggest effect sizes that are small to moderate, with 0.26 to .43 SD unit differences for primary parent-reported outcome of number of social needs and 0.38 to 0.46 SD unit differences for change in cortisol. A total sample of 724 dyads (n=362 per arm) will provide power to exceed 0.80 for tests on all primary outcomes. We conservatively estimate a 30% attrition rate over the course of the study, resulting in a final sample of 506 dyads post attrition (n=253 per arm). The study is powered at least 80% to detect small/medium effect sizes of d=.25 or greater. This sample size allows at least 80% power to detect estimated mean differences of changes from baseline of magnitude 0.50 or greater for our likert based primary outcome of number of social needs.

### 14.5 \* Eligible age range(s):

- ☒ 0-6 years
- ☒ 7-12 years
- ☒ 13-17 years
- ☒ 18+ years

### 14.6 Inclusion criteria:

- English or Spanish speaking parent or legeal gaurdian

- Parent or legal guardian accompanying an SFGH Primary Care or Urgent Care
- Clinic patient 0-17 years old
- Parent or legal guardian over or equal to 18 years old
- Parent or legal guardian resides with child in SF County
- Are not currently receiving services from the Health Advocate program or have not received Health Advocate services in the six months prior to enrollment

#### 14.7 Exclusion criteria:

- Non-English or non-Spanish speaking parent or legal gaurdian
- Parent or legal guardian under age 18
- Parent or legal guardian accompanying patient is not familiar with the child's living situation
- Currently receiving services from the Health Advocate program or have received Health Advocate services in the past six months
- Non-San Francisco resident
- Foster child or child in clinic for a child protective clearance exam
- In clinic for exam related to child abuse
- Clinic staff

#### 14.8 There are inclusion or exclusion criteria based on gender, race or ethnicity:

☐ Yes ☒ No

If **yes**, please explain the nature and rationale for the restrictions:

## 15.0 Other Approvals and Registrations

#### 15.1 \* Do any study activities take place on patient care units:

☒ Yes ☐ No

If **Yes**, attach a letter of support for the study from the involved patient care manager(s).

#### 15.2 \* Does your protocol involve any radiation exposure to patients/subjects? The UCSF Radiation Safety Committee requires review of your protocol if it includes administration of radiation as part of standard of care OR research exposures:

☐ Yes ☒ No

#### 15.3 \* This study may generate genetic data that may be broadly shared (e.g. submitted to NIH for Genome-Wide Association Studies (GWAS) in dbGaP, TCGA, etc):

☐ Yes ☒ No

#### 15.4 \* This study involves administration of vaccines produced using recombinant DNA technologies to human subjects:

☐ Yes ☒ No

#### 15.5 \* This study involves human gene transfer (NOTE: Requires NIH Recombinant DNA Advisory Committee (RAC) review prior to CHR approval):

☐ Yes ☒ No

**15.6 This study involves other regulated materials and requires approval and/or authorization from the following regulatory committees:**

☐ Institutional Biological Safety Committee (IBC)

Specify BUA #:

---

☐ Institutional Animal Care and Use Committee (IACUC)

Specify IACUC #:

---

☐ Radiation Safety Committee

Specify RUA #:

---

☐ Radioactive Drug Research Committee (RDRC)

Specify RDRC #:

---

☐ Controlled Substances

## 16.0 Procedures

**16.1 \* Procedures/Methods (Help Text updated 9/13) For clinical research list all study procedures, test and treatments required for this study, including when and how often they will be performed. If there are no clinical procedures, describe the Methods:**

All patients in ZSFG Peds Urgent Care during study hours meeting inclusion criteria will be asked by a designated study research assistant accompanied by a study designated trained SFGH Health Advocate Research Assistant (HARA) if they are interested in the study. (See Introduction Script attached.) If there is time in the urgent care private patient room (where there are often long waiting periods for providers), the research assistant will review consents and HIPAA authorization forms with family. Otherwise, following the clinic visit, the study research assistant will escort interested patient families to the ZSFG Health Advocate office on ZSFG 6A (on the same floor and down the hall from the urgent care clinic) for eligibility review and consent process. The study research assistant will assign eligible participants a study ID#, which will be stored in a password protected REDCap file on the study's encrypted and password-protected laptop.

The Research Assistant will review consent with eligible caregivers and patients old enough to participate in consent process. Consent will include documenting study ID, completing caregiver name and contact information and child MR#. (NB: Any duplicate MRN will not be eligible for participation.) One consent form will be used for participants randomized into the intervention arm or the control arm of the study (See attached).

Consenting caregivers will be given a copy of the study consent forms. They will also be asked to review and sign a HIPAA authorization form to enable access to separate ZSFG HA surveys/follow up and other health care records. In addition to caregiver consent, children 7 and older also will complete assent forms. (See attached study assent forms.) With caregiver permission, children will be offered entertainment activities including bubbles and age appropriate books, games, and videos. Before caregivers complete health surveys with the Research Assistant and HARA, children 2 yo and over and all caregivers will be given a cup of water and asked to swoosh mouths with water and then swallow water. This needs to be completed 20 minutes before saliva and buccal mucosal cell collection. Following water swoosh, all participating caregivers will complete a baseline survey conducted by Research Assistant and HARA on REDCap using a computer tablet. (See attached documents for baseline and follow up surveys.) There is one self-completion portion of the survey, which includes the Patient Health Questionnaire (PHQ-8) and measures for social support and stress, that participants can read and complete themselves or ask for assistance on. After completing the survey, all participating caregivers and children then will have hair cortisol and oral buccal mucosal cell and saliva samples collected. Participants will then be randomized into the intervention arm or the control arm of the study.

Randomization will occur at the participant level using a stratified randomization method in the computer-based program REDCap. This stratified method will be used to ensure a balance of Spanish speaking families and English speaking families within the groups. After completing the study survey and biomarkers collection, the Research Assistant will leave participant dyads with the HARA for randomization. The HARA will randomly assign participants to either the intervention or the control group. The Research Assistant will have no knowledge of or access to participants' group assignments.

If a family is randomized into the intervention group, the HARA will have access to the social needs screening results obtained through the health survey. The HARA will proceed with the health advocacy intervention following the procedures of the SFGH Health Advocacy program and attempt to address unmet needs identified by the caregiver in the survey. This involves working directly with these participants to identify and address any social needs the family may have such as access to food, living conditions and financial security. This may also include providing referrals to outside agencies, referral to legal aid within the clinic, help with applications for social benefits, or other services (See attached HARA Initial Action Plan and FollowUp Survey). Participants in the intervention group who are also ZSFG Pediatric Primary Care patients will have receipt of any direct assistance provided by the HARA documented in their child's medical record indicating services provided. All members of the intervention group will receive a written handout containing information about community resources related to the social needs we ask about in the survey.

The HARA will follow-up with members of the intervention group for a maximum of 3 months by telephone to continue to assess progress towards addressing social needs and to provide further help as needed. When relevant, HARA will send blank program forms to families or other publicly available program information via email or U.S. post to members of the intervention group. If a patient does not respond to telephone follow-ups for over 1 month, HARA may also send secure email to initiate follow-up contact.

If participant dyads are randomized into the control group, the HARA will provide the family with a written handout containing information about community resources related to the social needs we ask about in the survey.

Complete scripts for the biomarker specimen collections are found in Appendices A and B. Following surveys, hair, saliva and buccal mucosal cells will be collected non-invasively. These measures will be obtained immediately after enrollment and at the six month follow up timepoint.

